## Methods/Design

To answer the research questions in this proposed study, we will use a prospective longitudinal survey design. Study participants will be surveyed at regular intervals from the time they are referred for an elective surgical procedure until the time of their initial surgical consultation. For our purposes, this design is superior to cross-sectional surveys, where patients are asked retrospectively of their experiences. Retrospective studies are subject to recall bias and patients rate their health state higher as they adjust to limitations over time [17].

### Target population

Our sampling frame is those patients newly referred to a surgeon in one of the surgical specialties identified in Table 1 who are practicing in Vancouver, BC. The study will recruit patients referred for an elective surgical procedure from either primary care providers or from other specialties (i.e. cross-referrals). These surgical specialties have been selected for two reasons. First, they represent elective surgical procedures that can be considered preference-sensitive and non-surgical treatment options may be available. Second, we have pre-established relationships with surgeons in these surgical specialties through other studies. While there may be selection bias amongst those specialities that have agreed to participate, there is no reason to believe that patients of these surgeons are systematically different from the population as a whole.

**Table 1 Tab1:** **Procedures of interest by surgical specialty**

General surgery	Orthopedics	Plastic surgery	Urology
Laproscopic cholecystectomy	Elbow reconstruction	Breast reconstruction	Penile prosthesis
Femoral hernia repair	Knee ACL reconstruction	Mammoplasty reduction	Bladder suspension sling
Ventral hernia repair	Shoulder rotator cuff repair	Abdominoplasty	Urinary artificial sphincters
Inguinal hernia repair	Ankle arthritis	Hand tendon repair	Transurethral resection of the prostate
Gastrointestinal bypass	Bunion repair	Mandibular fracture	
Hemorrhoidectomies			

These surgeons have agreed to share their referral data with the study team. Patients will be contacted by the research team once the referral is received by the surgeon’s office. Though there will be a gap between the patient’s visit to the referring physician and the receipt of the referral by the surgeon’s office, we expect this gap to be less than seven days and to have a negligible effect on the study’s data.

### Sampling inclusion / Exclusion criteria

All patients who have been referred for an elective surgical procedure in Table 1, who are over the age of 18, and who are able to provide verbal and written consent in English will be recruited for the study. Patients will be excluded if they are facility-bound, are unable or unwilling to provide consent or if they demonstrate signs of severe depression or suicidal tendencies.

### Recruitment strategy

When a referral is received by the surgeon’s office, the patient will be asked by the office if they wish to be involved in this study. Patients that are interested will have their contact information securely transferred to a member of the study team. This team member will contact the patient over the telephone, explain the study, emphasize that it will have no impact on their wait time to see the surgeon and obtain verbal consent. Patients that provide verbal consent will be mailed a written informed consent with their initial survey.

### Survey

An initial survey package will be sent to participants and will include: 1) an information brochure outlining the study, 2) an informed consent form to be signed (in duplicate, so the participant may keep a copy), 3) contextual questions regarding their socio-demographic status [18] and most common co-morbidities and 4) questions reading their health status, knowledge about their condition and their decisional conflict (see Measures section below). Participants may opt out of any question(s) they are not comfortable answering. A self-addressed stamped envelope will be included in the package.

### Data collection procedures

The initial survey will be mailed as soon as verbal consent is received, within a week of the referral being received by the surgeon’s office. Subsequent surveys will be mailed every four months until the participant has their consultation with a surgeon. The last point of survey will be just before the surgical assessment. Patients may have different numbers of survey points because the WI period varies by speciality and surgeon. We will identify which patients progress to surgery with the assistance of the surgeon’s office.

### Survey management

A survey management database will be created for the purpose of organizing and coordinating the inbound and outbound survey packages. To cut down on labour needs, the data entry process will be automated by designing and printing surveys on scannable forms. Only the study’s principal investigator, survey coordinator and data entry staff will have access to the database. The statistician will have access to de-identified data.

### Participant retention

To enhance participant retention, reminders will be mailed out if survey packages are not returned within two weeks, followed by a telephone call if the survey package is still not returned.

### Sample size estimation strategy and power analysis

The study will contact each patient referred for a surgical assessment for the surgical specialties included in Table 1. Precise estimates of procedures for power calculations are derive from historical utilization patterns. Based on surgical utilization statistics, there were at least 200 procedures conducted in 2010/2011 for each urology procedure in Table 1, providing 200 potential study patients per year for each procedure, noting that Vancouver General Hospital and St. Paul’s Hospital act as a provincial referral centre for a number of specialized procedures, while other specialties have similar, or greater, number of potential study patients.

This pool of recruits provides a sampling frame of 700 patients for each procedure (of the four year study design, we will recruit patients for 3.5 years). Among these, we expect that we will recruit approximately 48% of patients, leaving the study with 336 patients per procedure. Given our experience in similar studies, we expect to retain 70% of patients throughout the observation period, or observe complete data on 235 patients (equal to 700 times 0.48 times 0.70).

The assumed effect size of 0.2 SD is inferred from previous studies. To detect a treatment effect size over the W1 time of 0.2 standard deviation (SD) on decline in health, and probability of proceeding to surgical treatment, our study will require 220 patients, presuming alpha = 0.05 (two-tailed) and beta = 0.20 (power = 80%). Therefore, relative to our projected recruitment, our study is adequately powered to detect moderate sized effects in each surgery.

### Consent and protection of confidentiality in data

To ensure confidentiality of data, all study participants will be provided a unique study identifier which will be kept physically separate from patient-identifying information. A computer file matching the patient to their unique study identifier will be encrypted and kept on a separate hard disk. This study has been approved by UBC’s Behavioral Research Ethics Board (BREB).

### Measures

Table 2 provides an overview of the survey instruments that will be used in this proposed study. These instruments were selected because they are short, validated questionnaires that will not overly burden participants and have no or minimal licensing costs. We chose those instruments that provide a single score that can be compared across time (intra-participant comparison) and participants (inter-participant comparison). All instruments will be administered to the participant for the initial (baseline) survey. Subsequent surveys will exclude the co-morbidity questionnaire.

**Table 2 Tab2:** **Patient reported outcome measure survey instruments and accompanying description**

Description	Instrument
**Generic assessment of health status**	EuroQol EQ-5D (5 L)
**Depression measure**	Patient Health Questionnaire (PHQ-9)
**Pain measure**	PEG-3
**Condition-specific assessment of health status**	Varies, depending on the procedure
**Assessment of medical and psychological syndromes**	Co-morbidity questionnaire
**Understanding of condition**	Knowledge questionnaire
**Sense of certainty with the treatment decision**	Decisional Conflict Scale

#### Generic assessment of health status

For the purposes of this study we use the EQ-5D-5 L to measure generic health status. The EQ-5D-5 L has been translated into 100 languages and is freely available to use, with no restrictions on publications. It is designed for self-completed post surveys and is easy to administer with minimal cognitive demands for study participants, taking only a few minutes to complete. The EQ-5D-5 L is widely used internationally and health states valuation norms have been validated in a Canadian population [19]. The EQ-5D-5 L has five questions addressing mobility, self-care, usual activities, pain/discomfort and anxiety/depression [19], which are scored using five levels. It also includes one vertical visual analogue scale on which the individual ranks their overall health status by making a mark along a line anchored by the endpoints labeled “best imaginable health state” and “worst imaginable health state”.

### Depression measure

To assess depression in patients’ we will use the Patient Health Questionnaire (PHQ-9). This instrument addresses both symptoms of depression and functional impairment [20]. There are nine questions regarding the presence of depression-related symptoms which are answered using a four-point Likert scale ranging from “not at all bothered” to “bothered nearly every day”.

### Pain measure

The PEG-3 will be used to assess pain in patients. The PEG has one intensity item and two interference items, for a total of three questions. Responses to the instrument’s three items are given a value between 0 and 10.

#### Assessment of medical and psychological syndromes

The research team has developed a questionnaire to assess the presence of common co-morbidities that may contribute to a patient’s clinical complexity. This questionnaire asks patients to report whether they have been diagnosed with common chronic, acute, or mental health conditions in the last three years. Responses to the questionnaire are not scored, rather they are used as a patient-level adjustment when analysing the study’s results.

#### Understanding of condition

A knowledge questionnaire asks patients about their understanding of their clinical problem, the treatment options available for that problem and the main benefits and potential side effects associated with those options. The knowledge questionnaires will be developed in conjunction with each of the participating specialities. Previous studies have generally developed a 6–8 item questionnaire using a multiple choice response format that have high degrees of internal consistency (alpha 0.82-0.83) and sensitivity to change [21–23]. These are scored based on the number of correct responses.

#### Certainty with treatment decision

The Decisional Conflict Scale will be used to assess a patient’s certainty about treatment. It is a validated, 16-item questionnaire [24]. Patients respond using a five item Likert scale, based on their level of agreement with a statement. High decisional conflict is associated with those patients who feel uninformed about their options, are unclear about their own personal values, or feel unsupported in making a decision.

### Preliminary data

To demonstrate the feasibility of recruiting patients into a study of this type and collecting patient-reported outcomes during the time that patients are waiting for surgical assessment, the study team conducted a pilot with orthopaedic surgeons in Vancouver. The study team worked with the surgeon’s staff to identify newly referred patients. A standardized script was prepared and used by the surgeon’s staff to summarize the study and describe the survey. Subsequently, patients were mailed a consent form and survey package. Completed packages were mailed to the surgeon’s office.

Fifty-five consecutive patients were contacted by the surgeon’s staff to determine whether they were willing to participate. Of those, three declined to participate and 52 surveys were mailed to patients. Of these patients, 27 ultimately returned the completed survey package with all assessment instruments completed, for a response rate of 48% (27 patients of 55 contacted).

The pilot of orthopaedic patients demonstrates the feasibility of collaborating with surgeon’s clinics to recruit patients newly referred to surgical assessment and to collect standardized patient health reported health, pain and depression measures during their wait.

## Discussion

There is an assumption in Canada that lengthy wait times for specialist consultations are an indicator of a poorly-performing healthcare system which can be resolved by expanding surgical supply or hospital capacity. In truth, there is little evidence regarding the effect of W1 on patients’ health and whether expanding surgical capacity would have any impact on outcomes. Given the investments federal and provincial stakeholders have made into improving access to elective surgical care, it is troubling that so little is known about the effects of waiting on patients’ health.

The conceptual model described above suggests that there is an opportunity to lower the W1 period. If there are specific characteristics that identify patients who are not certain of their decision to have surgery and are unlikely to proceed to surgery, yet still are on the wait list to be assessed by a surgeon, we could design algorithms to identify these patients in order to care for them in non-surgical ways. This would lower the wait time for those patients with appropriate referrals and improve the overall quality of healthcare by better matching treatments with patients’ preferences.

### Potential limitations

We are confident that this prospective longitudinal survey design is matched to meet the study’s objectives, but it has several limitations. These surveys suffer from sample attrition as patients drop out. Sample attrition is unavoidable in community-based studies, but through the use of reminders and communication with surgeons, we will take steps to mitigate attrition by making reminder calls and providing instructions to patients on how to update their contact information.

Self-selection bias is also a limitation of this survey design. We cannot be certain that those patients who opt out of the study do not systematically differ somehow from those that opt in. To address this we have allocated a significant budget to recruiting and following-up with participants.

Repeated questioning may cause participants to change their responses over time, a phenomena referred to as panel conditioning [25]. To mitigate this, we have minimized our survey points to every four months.

### Potential outcomes and future applications

This study will provide evidence to confirm or invalidate the theory that waiting for surgical assessment for elective surgeries is associated with negative consequences for patients’ health. If the results from this study do not indicate that waiting for elective surgical assessment has significant consequences for patients’ health, then this study challenges perceptions regarding wait times.

The knowledge gained from this study can be used to inform both policy-makers and clinicians regarding the health impact of waiting. For policy-makers, evidence from this study may form a foundation for decisions to brake (or accelerate) policy interventions designed to expedite surgical access. For clinicians, this study could identify opportunities to reduce inappropriate referrals for elective surgery either through better patient education interventions or improved shared decision-making.

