### Objective

The objective of this proposed study is to understand the impact that W1 for elective surgeries has on the health of patients and to determine whether this time can be reduced. This objective will be met by answering four research questions:What is the length of time patients spend waiting for their initial surgical assessment?What is the change in health status that patients experience while waiting for their initial surgical assessment?What are patient factors associated with the decision to proceed with surgery?Does self-reported information help to discriminate between warranted and unwarranted referrals?

This study is being undertaken in collaboration with several surgical groups practicing in Vancouver Coastal Health (VCH) authority. This research team has strong historical relationships with many specialty surgical groups practicing in VCH’s six hospitals, the VCH executive team and the British Columbia (BC) Ministry of Health, ensuring the study’s feasibility and maximizing the likelihood that the findings from this study will be incorporated into decision- and policy-making processes.

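### The conclusion planned for a null result is stronger than a single cohort powered only to detect a 0.2 SD decline per procedure can support

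*Protocol article*

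**What the plan says.** The Objective section sets out to "understand the impact that W1 for elective surgeries has on the health of patients". The research question that serves this aim is narrower: "What is the change in health status that patients experience while waiting for their initial surgical assessment".

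The Methods/Design section describes one cohort: "Study participants will be surveyed at regular intervals from the time they are referred for an elective surgical procedure until the time of their initial" visit to the surgeon. It describes no group that does not wait or that is set up to wait less. In arguing against retrospective surveys, the same section notes that "patients rate their health state higher as they adjust to limitations over time".

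The section on sample size and power gives one target: "To detect a treatment effect size over the W1 time of 0.2 standard deviation (SD) on decline in health", with two-sided alpha 0.05 and 80% power. It states a need for 220 patients and expects 235 complete cases per procedure.

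The section on potential outcomes and future applications then says: "This study will provide evidence to confirm or invalidate the theory that waiting for surgical assessment for elective surgeries is associated with negative consequences". If the results "do not indicate that waiting for elective surgical assessment has significant consequences for patients’ health, then this study challenges perceptions regarding wait times". For policy-makers, it adds that "evidence from this study may form a foundation for decisions to brake (or accelerate) policy interventions designed to expedite surgical access".

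The limitations section names attrition, self-selection and panel conditioning. It mentions neither the missing comparator nor how a null result should be read.

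**The concern.** Two gaps separate the planned evidence from the announced conclusion.

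The first is statistical. A study sized to detect a difference does not show that the difference is small merely by failing to detect it. What a null result rules out depends on the confidence interval, and the text gives no such standard where it says what a null would mean.

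The second is one of design. Change from referral to assessment is not the effect of waiting. It also contains the natural course of the condition, regression to the mean from a visit that may have been prompted by worse symptoms, and adaptation. The last two can mask a decline, while natural progression can imitate an effect of waiting. A larger sample removes none of this.

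At stake is what the study may tell those who fund surgical access. A null that is only imprecise could be taken as evidence against harm, and an observed decline could be put down to waiting without support.

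**Working it through.** **Inputs from the power section:** effect 0.2 SD; alpha 0.05 two-sided; power 80%; 220 required; 235 expected complete cases per procedure. **Assumptions:** 0.2 SD is in units of the SD of change, and a paired test stands in for the repeated-measures model.

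**1. The plan's own figures.** 700 × 0.48 × 0.70 = 235.2, so 235 reproduces. For a paired change, n = ((1.960 + 0.842)/0.2)² gives 197 (199 with the t distribution), so 220 does not reproduce from the stated inputs. It errs on the safe side for this test (84% power), and nothing below depends on it.

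**2. Precision.** The 95% half-width is 1.96/√235 = 1.96/15.33 = 0.128 SD. A decline that just misses significance is therefore estimated at 0.128 SD, with an upper limit of 2 × 0.128 = 0.256 SD. That is above the 0.2 SD target. With 220 patients the figures are 0.132 and 0.264.

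**3. Chance of a non-significant result, n = 235.** The normal form is approximately Φ(1.96 − d√235); the last column uses the paired t-test.

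| True decline d | d√235 | Normal | Paired t |
|---|---|---|---|
| 0.10 SD | 1.533 | 0.665 | 0.667 |
| 0.15 SD | 2.299 | 0.367 | 0.371 |
| 0.20 SD | 3.066 | 0.134 | 0.137 |

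The last row is ordinary type II error and lies within the planned 20%. The first two rows show how often smaller true declines would go undetected.

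**4. What an interval-based reading would do.** The 95% interval excludes a 0.2 SD decline when the estimated decline is below 0.200 − 0.128 = 0.072 SD. Estimates between 0.072 and 0.128 SD are non-significant yet do not exclude 0.2 SD. If the true decline is 0.10 SD, about 33% of analyses fall in that band. If there is no true change, the interval excludes 0.2 SD with probability Φ(0.2√235 − 1.96) = Φ(1.106) = 0.87.

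**5. Sensitivity to the unit of the SD.** If 0.2 SD refers to raw scores, the SD of change is √(2(1 − r)) raw SDs, where r is the within-patient correlation. The document does not give r, so the values below are assumed.

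| r | SD of change | Half-width | Upper limit, just non-significant |
|---|---|---|---|
| 0.3 | 1.183 | 0.151 | 0.303 |
| 0.5 | 1.000 | 0.128 | 0.256 |
| 0.7 | 0.775 | 0.099 | 0.198 |

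At r = 0.7 the miss rates for 0.10, 0.15 and 0.20 raw SD fall to about 49%, 16% and 2%. The size of the problem therefore depends on a unit that the power section does not state.

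**6. Pooling.** Table 1 lists 6 + 5 + 5 + 4 = 20 procedures. If all reached 235 and were pooled (an assumption), n = 4,700 and the half-width is 1.96/√4,700 = 0.029 SD. The figures in steps 2 to 4 hold for one procedure at a time, the level at which the plan claims its power.

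**7. Attribution.** The document gives no means of sizing natural course, regression to the mean or adaptation, so no figure is offered.

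**The case against.** The strongest reply is that this is discussion prose, not an analysis rule. A reader might infer that the plan will declare waiting harmless whenever p exceeds 0.05. The documents do not support that: the text speaks of challenging perceptions, never says waiting does no harm, and does not tie the word significant to a p-value. Nor may one infer that a null result would by itself halt access programmes. The policy sentence is hedged, runs in both directions and is not attached to a null.

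It can also be said that margins and model details belong in an analysis plan that is not shown. That is fair, and the absence of a margin is not the point here. The point is what the article does say: that the study can invalidate the theory, and that a null has a particular meaning.

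The article also offers more than a simple before-after comparison. It plans repeated-measures models with surgeon effects, comorbidity adjustment and four-monthly surveys over waits that vary by specialty and surgeon, and a single cohort can answer the question about change while waiting. This stands. But varying wait length is not set up as a comparison of longer with shorter waits, so the aim of understanding impact is not yet met.

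Pooled analyses would be far more precise, so the miss rates must not be read as applying to the study as a whole. Pooling would not cure the attribution problem. Finally, the adaptation remark is aimed at retrospective surveys. Applying it to repeated ratings is a reasonable inference, but it is ours.

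**Conclusion.** The point holds as a mismatch between the conclusions announced and what the design and sample can show. For a single procedure with 235 complete cases, a non-significant result can leave open a decline of about 0.256 SD, beyond the plan's own 0.2 SD, and a true decline of 0.10 SD would be non-significant about two times in three. These sizes assume that 0.2 SD is on the scale of the SD of change, that the expected number of complete cases is reached and that analysis is by procedure. On a raw-score scale with high within-patient correlation, or with pooling, the precision problem shrinks. The attribution problem does not depend on any of these: with no comparator, mean change alone cannot tie either a null or a decline to waiting, and the limitations section should say so. Data collection is unaffected, so this is a matter that should be corrected rather than one that endangers the study.

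**What to change.** 1. In the section on potential outcomes, replace the claim to confirm or invalidate and the sentence on a null result with an interval-based statement. For each procedure, conclude that a decline as large as the plan's own 0.2 SD is ruled out only if the 95% confidence interval for change excludes it; report any other non-significant result as inconclusive. State whether the SD is that of change or of raw scores. The 0.2 SD is used because it is the plan's only threshold; this does not show that smaller declines are unimportant.
2. Present mean change during W1 as descriptive. Address the impact objective by adding W1 length to the planned repeated-measures models, adjusted for baseline score, procedure and comorbidity. Report the result as an association open to confounding by urgency and case mix. Differences between surgeons in typical wait should not be relied on to remove that confounding: surgeon effects are already in the models and waits vary by specialty.
3. Add the missing comparator to the limitations.

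The cost is some rewording and a little more analysis of data already being collected. No extra patients are needed for the 0.2 SD criterion. The downside is that some null results will have to be reported as inconclusive.
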